### Study designs

EITRS is a randomized, double-blind, multi-center clinical study with two parallel arms in 1:1 ratio to evaluate the efficacy and safety of idebenone in patients with iRBD compared with placebo. The total study duration of 6 years comprises a 1-year enrollment period and a 5-year intervention period. One hundred forty-two eligible participants will be allocated to idebenone or placebo group randomly and equally after baseline assessment. Follow-up evaluations will be conducted at the 1st, 3rd and 5th years of treatment in any of the three centers to detect the disease progression. Routine blood testing and liver function will be monitored every 6 months during the administration. Participants, investigators and statisticians are masked to the allocation code. The flowchart of the trial is outlined in Figure 1. The EITRS study is registered with ClinicalTrial.gov (Register Number: NCT 04534023).

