### Inclusion criteria

Male or female, aged 40–75;The diagnosis of RBD was confirmed by polysomnography (PSG) according to standard criteria published by the American Academy of Sleep Medicine in the International Classification of Sleep Disorders (ICSD) III (26);Patients voluntarily participated in this study and signed informed consent with good compliance.

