### Exclusion criteria

PSG-confirmed sleep apnea hypopnea syndrome, which includes but not limited to obstructive sleep apnea syndrome (apnea/hypopnea index >5) (26);Patients with symptoms including bradykinesia, myotonia, tremor or posture instability;Previous history of sudden withdrawal of sedative or psychotropic drugs prior to the onset of the symptoms;Previous history of neurological diseases such as cerebral hemorrhage, cerebral infarction, brain trauma, brain tumor or central nervous system infection;Previous history of sleep disorders or seizure;Alcohol or drug dependence (addiction).

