
### Outcome measures

The primary outcome is the comparison of conversion rate from iRBD to synucleinopathies between idebenone and placebo group, measured at 5-year of follow-up. Clinical symptoms will be evaluated by physicians using comprehensive rating scales. PET/MRI will be carried out to reflect the dopaminergic degeneration. The secondary outcome is the safety and tolerability of idebenone in the treatment of patients with iRBD. The objects for safety evaluation should contain all the participants that have been administrated with the experimental drug. Safety evaluation including the laboratory test results, the events of death and adverse reactions, will be recorded in detail and analyzed after the trial (Table 1).

**Table 1 T1:** Outcome measures taken at baseline and follow-up.

**Endpoint**		**Measure**	**Evaluating methods/criterion**	**Time points**
Primary	Effectiveness: 5-year conversion rate of iRBD into synucleinopathies	Rating scales	MDS-UPDRS, RBDSQ, MMSE, MoCA, SS-16, HAMD-17, NMSQ, SCOPA-AUT	Baseline, 1, 3, 5 years
		Blood testing	Biomarkers including neuronal exosomal α-synuclein, SNCA methylation, inflammatory cytokines and chemokines (IL-8, TNF-α, TGF-β, IL-10, IL-6, CXCL12, CX3CL1, CCL15, CCL3 and CCL20)	
		Neuroimaging examinations	(^18^F-FP-CIT) DAT-PET/ MRI	
Secondary	Safety and tolerability	Vital signs	Body temperature > 39.5°C, pulse rate <50 beats/min, blood pressure < 80/60 mmHg, blood pressure > 220/120 mmHg, oxygen saturation < 90%;	Every 6 months
		Electrocardiogram	Atrial fibrillation, complete atrioventricular block, sinus arrest, ventricular tachycardia, ventricular fibrillation, pathologic Q-waves, arched ST-segment elevation	
		Laboratory tests	The ratio of alanine aminotransferase to aspartate aminotransferase over twice the normal values after treatment, the creatinine over twice the normal value, glomerular filtration rate lower than 20 ml/min, red blood cell, hemoglobin, white blood cell and platelet count <50% of the lower normal limit or more than twice the upper normal limit	
		Adverse events	Result in death, are immediately life-threatening or cause severe organ damage	

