### Sample size and statistical analysis

The 5-year conversion rate of participants treated with idebenone is expected to decrease from 47% in the placebo group to 25%. The idebenone and placebo group are randomized at a ratio of 1:1, and a 5% drop-out rate is considered throughout the study. We estimated that 71 patients would be needed in each treatment group to allow for a power of 80% at two-sided α-level of 5%. In total, 142 patients are projected to be enrolled.

Statistical analysis will be performed using SPSS 27.0, STATA 17.0 and GraphPad Prism 9.4.0. Data will be analyzed on an intention-to-treat basis using two-sided tests with *p* < 0.05 considered significant. Continuous variables will undergo normality test as well as ANOVA test for inter-group comparison. Categorical variables will be compared using Chi-square test, Fisher's exact test or Wilcoxon rank-sum test. To assess the five-year conversion rate from iRBD diagnosis to clinically diagnosed synucleinopathies between patients treated with idebenone and placebo, we estimated the hazard ratio (HR) using a Cox proportional hazards model. Kaplan-Meier method will be applied to estimate median progression-free survival (PFS) and corresponding 95% confidence interval (CI) and survival curves will be plotted.

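### Time zero for the primary time-to-event analysis is stated inconsistently: from iRBD diagnosis in the analysis text, from the start of follow-up or treatment elsewhere

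*Protocol article*

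**What the plan says.** All references are to the protocol article.

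- *Sample size and statistical analysis* states the purpose of the primary model as "To assess the five-year conversion rate from iRBD diagnosis to clinically diagnosed synucleinopathies" in the two arms, and continues "we estimated the hazard ratio (HR) using a Cox proportional hazards model". Kaplan-Meier curves are planned as well. No time zero is given for either method, and delayed entry is not mentioned.
- *Outcome measures* defines the primary outcome as the comparison of conversion "between idebenone and placebo group, measured at 5-year of follow-up".
- *Study designs* says the study "comprises a 1-year enrollment period and a 5-year intervention period" and that "Follow-up evaluations will be conducted at the 1st, 3rd and 5th years of treatment". *Endpoint criteria* closes a patient's participation at completion of five years of treatment or at conversion.
- *Inclusion criteria* requires that "The diagnosis of RBD was confirmed by polysomnography (PSG) according to standard criteria", with no limit on how long ago. *Exclusion criteria* removes "Patients with symptoms including bradykinesia, myotonia, tremor or posture instability".

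**The concern.** A time-to-event analysis needs one origin. The only origin that the analysis section names is the iRBD diagnosis, which precedes randomisation by an interval that the article neither states nor limits. Because patients with motor signs are excluded at entry, that interval is largely free of conversion by selection.

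If the clock starts at diagnosis and patients count as at risk from then on, each contributes event-free time before treatment begins. Two things follow. The five-year Kaplan-Meier rate falls below the five-year rate of follow-up on which the trial was sized (47% against 25%). When the lag varies between patients, the risk sets also include people not yet randomised, who cannot have an event. That dilutes the comparison and costs some power in a trial planned at 80%.

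**Working it through.** **Inputs from the article.** Five-year conversion 47% (placebo) and 25% (idebenone); 71 per arm, 1:1; two-sided 5%; 80% power; five years of treatment per patient.

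**Assumptions, not in the article.** Constant conversion hazard in each arm from randomisation; a diagnosis-to-randomisation lag of 0.5 to 3 years; no drop-out in the simulation.

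**1. The plan's own figure.** HR = ln(0.75)/ln(0.53) = 0.453. The Schoenfeld formula gives 4 × (1.960 + 0.842)² / (ln 0.453)² ≈ 50.1, so 51 events. At an average conversion of (0.47 + 0.25)/2 = 0.36, that is 51/0.36 = 141.7 patients, or 71 per arm. This matches the stated 71 before any drop-out allowance; adding 5% gives 75. That gap is a separate matter. The relevant point is that 71 fits 47% and 25% counted over five years of follow-up.

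**2. Same lag L for everyone, closed form.** Hazards are −ln(0.53)/5 = 0.1270 and −ln(0.75)/5 = 0.0575 per year. Without delayed entry, conversion at five years from diagnosis is 1 − exp(−hazard × (5 − L)). For L = 1:

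- placebo: 1 − exp(−0.1270 × 4) = 39.8%
- idebenone: 1 − exp(−0.0575 × 4) = 20.6%

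| Lag (years) | Placebo | Idebenone |
|---|---|---|
| 0 | 47.0% | 25.0% |
| 0.5 | 43.5% | 22.8% |
| 1 | 39.8% | 20.6% |
| 2 | 31.7% | 15.9% |
| 3 | 22.4% | 10.9% |

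A common lag shifts every event time by the same amount, so the risk sets and the Cox hazard ratio do not change.

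**3. Lag varying between patients.** 1,500 simulated trials per setting, 71 per arm, exponential lag, everyone followed five years from randomisation and all events used. Each trial was analysed from randomisation and from diagnosis without delayed entry.

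| Mean lag (years) | Kaplan-Meier at 5 years from diagnosis, placebo/idebenone | HR: randomisation → diagnosis | Cox power: randomisation → diagnosis |
|---|---|---|---|
| 0.5 | 43.5/22.7% | 0.446 → 0.446 | 80.1 → 80.1% |
| 1 | 39.3/20.7% | 0.453 → 0.456 | 78.6 → 77.1% |
| 2 | 31.8/16.3% | 0.445 → 0.457 | 80.3 → 75.1% |
| 3 | 26.0/13.4% | 0.446 → 0.467 | 79.8 → 72.8% |

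From randomisation, the Kaplan-Meier rates in the same data were 47.0–47.2% and 24.9–25.2%. The Monte Carlo standard error of each power figure is about √(0.8 × 0.2/1500) = 1.0 percentage point.

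**4. Diagnosis clock with delayed entry at randomisation.** The HR was 0.445–0.452, power 78.3–80.3%, and the placebo Kaplan-Meier rate 46.6–47.1%. The distortion largely disappears, so its source is the uncorrected time before randomisation. The return to 47% also relies on the constant hazard assumed here.

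**The case against.** The best counter-argument is that the phrase describes a transition and not a clock. *Outcome measures* and Table 1 speak of conversion from or of iRBD into synucleinopathies, and the analysis sentence may be a longer form of the same expression. Everything else in the article ties the five years to treatment or follow-up, and a condensed article may leave the exact origin to an analysis plan. Much of this stands: a diagnosis-started clock is a possible reading, not an established plan. It does not remove the point. The sentence attaches a datable event to a five-year rate in front of a model that needs an origin, and the origin it names differs from the endpoint's. That is a conflict in the text, not a detail left out.

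The lag is also unknown. If the confirming polysomnography is done at or near screening, the effect is close to nil. This stands too, and is why only a range can be given.

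A reader might infer three stronger things that the documents do not support:

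- **That conversion-free time before randomisation biases the comparison towards idebenone.** Time since diagnosis is a baseline characteristic, balanced between arms in expectation by randomisation. What shift there is goes towards the null.
- **That the hazard ratio is materially attenuated.** The largest movement found was from 0.446 to 0.467, at a mean lag of three years.
- **That events later than five years after diagnosis would be discarded, with heavy loss of power.** No section states such a cut-off, and *Study designs*, *Endpoint criteria* and *Outcome measures* all run follow-up to five years of treatment.

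**Conclusion.** The inconsistency is real and should be corrected, but it does not threaten the validity of the treatment comparison. It matters only if the analysis sentence is applied literally and without delayed entry. The main damage would then be to the absolute five-year Kaplan-Meier rates: roughly 4 percentage points off the placebo figure at a mean lag of half a year (47 − 43.5 = 3.5) and 21 at three years (47 − 26.0). They would no longer be comparable with the rates used for sizing. Power would be unchanged at half a year and about 7 points lower at three years (79.8 − 72.8). The crude proportion converted by five years of follow-up does not depend on the clock.

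The sizes rest on an assumed lag, which the documents do not give, and on constant hazards. The direction for the absolute rates needs only some conversion-free interval between diagnosis and randomisation.

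**What to change.** Reword the analysis sentence so that the five-year conversion rate is counted from randomisation instead of from iRBD diagnosis, and state that the randomisation date is time zero for both the Cox model and the Kaplan-Meier curves. If time since diagnosis is wanted as the time scale, say so and have patients enter the risk set at randomisation (delayed entry). If disease duration is of interest only as a prognostic factor, it can be a baseline covariate instead.

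The cost is one sentence in the protocol, carried into the analysis plan, with no change to data collection or sample size. It should be settled before unblinding, so that the choice of origin cannot depend on the results.

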## Discussion

iRBD is a REM sleep parasomnia, affecting ~1% of the elderly population and compromising quality of life profoundly (1). Given the increasingly well-recognized link between iRBD and α-synuclein-specific neurodegeneration, a strong rationale exists for considering the population of patients with iRBD as ideal for testing possible disease-modifying strategy. Idebenone is a well-described drug that was initially developed against cognitive decline. It is a synthetic quinone with similarities to the naturally occurring CoQ10 (37). Beneficial effects of idebenone have been reported in the clinical trials of some neurodegeneration diseases, including Huntington's disease, Alzheimer's disease, dementia and Friedreich ataxia (38–41). Besides, rare adverse effects of idebenone mainly include allergic reactions, rashes, nausea, loss of appetite, diarrhea, excitement, insomnia, dizziness, etc. with great tolerability and compliance of patients (42). Recent studies revealed that idebenone ameliorated motor dysfunction by regulating mitophagy in MPTP-induced PD mice (21, 22). Other non-motor symptoms such as sleep disorder, autonomic dysfunction, cognitive and psychiatric impairment can also be improved. The underlying mechanisms are multitudinous and comprehensive, including the regulation of 5-hydroxytryptamine neurotransmitter and hippocampal function, the protection against oxidative stress injury, the inhibition of apoptosis signal and the activation of mitochondrial function (20, 43). It seems that a novel indication of idebenone is promising on preventing or delaying neurodegeneration with its favorable safety and tolerability profiles when administrated in a prodromal stage.

In this paper, we outlined our rationale and design of the EITRS study. The EITRS study is a randomized, double-blind, multi-center clinical study is to identify the efficacy and safety of idebenone in the treatment of iRBD into synucleinopathies initially. Three centers participate in the trial and the first patient has been recruited into the study in July 2020. The study is leaded by Ruijin Steering Committee. The Steering Committee members and principal investigators of each center are in charge of the ethics and patient safety. They will have a face-to-face or online meeting to supervise the status and progress of the trial. The diagnosis of iRBD and α-synucleinopathies will be reviewed by independent experts in each center and steering committee. The sponsor of the EITRS trial is the Clinical Research Center, Shanghai Jiao Tong University School of Medicine. The results are expected for publications in 2026.

## Ethics statement

The studies involving human participants were reviewed and approved by Ethics Committees of the Ruijin Hospital affiliated with Shanghai Jiaotong University School of Medicine. The patients/participants provided their written informed consent to participate in this study. Written informed consent was obtained from the individual(s) for the publication of any potentially identifiable images or data included in this article.

## Abbreviations

REM: rapid eye movement
RBD: REM sleep behavior disorder
iRBD: idiopathic RBD
PD: Parkinson's disease
DLB: dementia with Lewy bodies
MSA: multiple system atrophy
RSWA: REM sleep atonia loss
18F-FDG PET: ^18^F-flurodeoxyglucose positron emission tomography
1^2^3I-FP-CIT SPECT: ^123^I-N-ω-fluoropropyl-2β-carbomethoxy-3β-(4-iodophenyl) nortropane single-photon emission computed tomography
MRI: magnetic resonance imaging
DAT: dopamine transporter
PSG: polysomnography
AE: serious adverse event
SAE: serious AE
HR: hazard ratio
PFS: progression-free survival
CI: confidence interval
ICSD: International Classification of Sleep Disorders
MDS-UPDRS: Movement Disorder Society-Unified Parkinson's Disease Rating Scale
RBDSQ: REM sleep behavior disorder screening questionnaire
MMSE: Mini-Mental State Examination
MoCA: Montreal Cognitive Assessment
SS-16: Sniffin’ Sticks test-16
HAMD-17: 17-Item Hamilton Rating Scale for Depression
NMSQ: Non-Motor Symptom Questionnaire
SCOPA-AUT: Scales for Outcomes in Parkinson's Disease-Autonomic questionnaire
IL: interleukin
TNF: tumor necrosis factor
CXCL: C-X-C motif ligand
CX3CL1: C-X3-C motif ligand 1
CCL: C-C motif ligand.
